### Study outcomes

Primary outcomes of this clinical trial are the changes in anthropometric indices (including weight, BMI, hip circumference, waist-to-hip ratio, fat mass, muscle mass) and food addiction score. Secondary outcomes are changes in stress level, eating behavior, and serum levels of BDNF and LBP.

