In order to measure blood biochemical parameters, 5 cc of venous blood samples will be taken from the site of the bracing vein and after 12 to 14 h fasting by the laboratory technician at the beginning and the end of the study. Blood samples taken in tubes containing sodium citrate anticoagulants will be collected and centrifuged in the laboratory of the Shahid Beheshti Nutrition Faculty for 15 minutes at a speed of 500 rounds per minute and serums will be stored at − 80°C until the tests are performed. Serum levels of BDNF and LBP will be measured by the ELISA method with a human BDNF kit (PadginTeb, under the license of Zelbio, Iran) and a human LBP kit (PadginTeb, under the license of Zelbio, Iran) with the intra-assay and inter-assay CV of < 10% and <12%, respectively, for both kits in the laboratory of the Nutrition Institute of Shahid Beheshti University of Medical Sciences.

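### As written, the BDNF samples get a spin of only about 28 to 56 g, too weak to clear platelets from citrate plasma; the speed needs confirming and stating in g

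*Protocol article*

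**What the plan says.** The handling of the blood is described under Study outcomes:

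- Sample: "5 cc of venous blood samples will be taken from the site of the bracing vein", at the start and the end of the study.
- Tube: "Blood samples taken in tubes containing sodium citrate anticoagulants".
- Spin: "centrifuged in the laboratory of the Shahid Beheshti Nutrition Faculty for 15 minutes at a speed of 500 rounds per minute". No force in g and no rotor radius are given, and no second spin or filtration is described.
- Storage: "serums will be stored at − 80°C until the tests are performed".
- Assay: "Serum levels of BDNF and LBP will be measured by the ELISA method". The intra- and inter-assay CVs are given as below 10% and below 12% for both kits.

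The same section gives the role of these markers: "Secondary outcomes are changes in stress level, eating behavior, and serum levels of BDNF and LBP". The Abstract and the Discussion present BDNF as the route by which time-restricted feeding might act on eating behaviour and weight.

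**The concern.** Blood in a citrate tube does not clot, so no clot holds the platelets back. Whether they leave the plasma depends on the spin. The article gives a definite operating value for that spin, and the value looks far too low to yield a cell-free sample. Platelets left in the supernatant are frozen with it and can be expected to break on thawing.

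Two links here are general laboratory knowledge and not statements in the document: that platelets carry BDNF, and that freezing and thawing releases their content. If both hold, the measured value mixes BDNF circulating in plasma with BDNF from however many platelets were pipetted. The sample would be neither serum nor cell-free plasma. The quoted CVs describe the precision of the assay and would not cover this variation, which arises before the assay. With 30 women enrolled per group, extra noise in a change score is costly.

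**Working it through.** The document gives no force, so there is no figure of its own to reproduce. The check asks what force the stated speed produces.

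**1. Force**

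Force (g) = 1.118×10⁻⁵ × radius (cm) × (rounds per minute)²

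At 500 rounds per minute: 1.118×10⁻⁵ × 500² = 2.795 g per cm of radius. The radius is an assumption.

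| Assumed radius (cm) | Force at 500 rpm (g) |
|---|---|
| 5 | 14 |
| 10 | 28 |
| 15 | 42 |
| 20 | 56 |
| 25 | 70 |

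Reaching 1000 g at this speed would need a radius of 1000 / 2.795 = 358 cm, about 3.6 m. The finding of a weak spin therefore does not depend on the radius assumed.

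**2. How far platelets settle in 15 minutes (900 s)**

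Stokes velocity: v = d² × Δρ × (9.81 × force) / (18 × viscosity). The platelet and plasma properties are assumptions. The formula treats platelets as isolated spheres, so it gives an order of magnitude only.

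- Central inputs (Δρ 35 kg/m³, viscosity 1.2 mPa·s): 1.6 mm for a diameter of 2 µm at 28 g, and 7.2 mm for 3 µm at 56 g.
- Wider inputs (Δρ 15 to 40 kg/m³, viscosity 1.3 mPa·s, same diameters and forces): 0.6 to 7.6 mm.

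**3. Share left in the supernatant**

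Share = 1 − settling distance / height of the plasma column. The height is also an assumption.

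- 30 mm column, central inputs: 1 − 7.2/30 = 76% to 1 − 1.6/30 = 95%.
- 30 mm column, wider inputs: 1 − 7.6/30 = 75% to 1 − 0.6/30 = 98%.
- 20 mm column, wider inputs: 1 − 7.6/20 = 62% to 1 − 0.6/20 = 97%.

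**4. Comparison with a stronger spin**

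At 3000 rounds per minute the force is (3000/500)² = 36 times larger: 1006 g at 10 cm and 2012 g at 20 cm. The smallest central settling distance becomes 1.6 × 36 = 58 mm, more than the whole 30 mm column. Under the slowest of the wider inputs it is 0.63 × 36 = about 23 mm, which is not quite the whole column. So 1000 g is an order of magnitude, and the exact force has to come from the kit instructions.

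**The case against.** **The argument depends on the tube.** The article calls the analyte serum throughout, and a single clause names citrate. If the blood is really allowed to clot, the platelets are held in the clot and the carry-over argument lapses. This stands, so the point can only be made conditionally. A reader might infer that the samples will certainly contain platelets. The document does not support that, because its own wording on the sample type conflicts.

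**The speed may be a reporting slip.** The surrounding text is loosely worded, and 500 could be a typing error or a force in g labelled as a speed. That is possible, and it makes confirming the speed the first step. It does not remove the need for a correction. With a dropped zero (5000 rounds per minute) the force would be 2795 to 5590 g at 10 to 20 cm, and the concern would go. As a force of 500 g, the slowest settling would be 0.63 × 500/28 = about 11 mm of an assumed 30 mm, so clearance would still be open to doubt.

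**Rotor radius is laboratory-manual detail.** Agreed: a condensed article may leave it out, and its absence is not the point here. The point is that the value the article does state cannot do the job at any realistic radius.

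**The consequence is easily overstated.** A reader might infer that no BDNF result could be interpreted, that the arms would be biased, that batches would shift, or that LBP is affected too. The document supports none of these:

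- One procedure is described for everyone, and allocation is randomised. The main effect is therefore noise, which weakens a null result but does not make a difference between arms meaningless.
- No batch plan is described from which a shift could be shown.
- The Background describes LBP as produced by the liver, and the platelet argument does not reach it.
- The primary outcomes (anthropometry and food addiction score) are untouched.

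**Conclusion.** The point holds in conditional form. The stated spin gives about 28 to 56 g at an assumed 10 to 20 cm, and no more than about 70 g at 25 cm. If the tubes are citrate and the speed is as printed, most platelets remain in the frozen plasma under the settling inputs assumed, and BDNF will include a variable platelet contribution. That last step rests on general laboratory knowledge.

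The size of the effect on the BDNF variance cannot be worked out from the document. Its kind can: added noise and uncertainty about what is being measured, in one secondary outcome. This is worth correcting because a specific operating value is wrong for its purpose and the correction is cheap. It does not threaten the trial's primary conclusions.

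**What to change.** 1. Confirm the speed and the tube actually used.
2. Correct the sentence under Study outcomes so that sample type and spin agree. Resolve the conflict between citrate tubes and serum, and state the spin as a force in g that gives a cell-free sample according to the BDNF and LBP kit instructions. The order of magnitude is 1000 g or more, to be confirmed from the kits.
3. If the printed speed was only a reporting error, nothing more is needed.
4. If samples were really spun at 500 rounds per minute:
   - Flag them in the data set.
   - Where possible, handle a participant's baseline and week-8 samples the same way. Changing the setting between them would put a handling difference inside the change score, which is the outcome itself.
   - Add a BDNF sensitivity analysis that leaves out participants with any sample spun at 500 rounds per minute or with different handling at the two time points. If that leaves too few to analyse, report the handling as a limitation of the BDNF result.

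**Cost.** The correction is one sentence and, if needed, one centrifuge setting. The real cost falls on the sensitivity analysis. Recruitment began in November 2021, so some samples may already have been processed, and every participant left out reduces a trial planned on 26 evaluable women per group.

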### Assessment of dietary intake

In this study, to assess participant’s dietary intake, at the beginning of the study, at the end of the fourth and eighth weeks of the study, 3 days of dietary recall about one weekend day and two week days will be completed through face-to-face or telephone interviews. Common household measurement tools (glass, cup, soup bowl, plates, teaspoon, and tablespoon) will be provided to assist subjects in estimating the portion size of the food. Dietary intake will be analyzed using Nutritionist IV (N4) software.

### Assessment of physical activity level

Physical activity questionnaire will be completed for them at baseline and week 8 [32]. This questionnaire is divided into 9 levels based on the intensity of physical activity and metabolic equivalents (MET) and its rows are adjusted from top to bottom from inactivity (MET = 0.9) to intense activities (MET >6). The intensity of activities from top to bottom is 0.9, 1, 1.5, 2, 3, 4, 5, 6, and above 6, respectively. These numbers are multiplied by the duration of the activity to show the intensity of the activity performed per time unit (MET.time).

### Statistical analysis

In this study, data analysis will be performed by using SPSS version 21.0 (SPSS Inc, Chicago, Illinois) software. Paired *t* test will be used to compare the mean of quantitative variables with normal distribution in each group between the beginning and the end of the study and the *t* test will be used to compare their mean between the two groups at the beginning and end of the study. In the case of quantitative variables with non-normal distribution, Wilcoxon and Mann-Whitney tests are used, respectively. In case of the variables measured three times during the study (beginning, fourth week, and eighth week), repeated ANOVA test will be used. Covariance analysis will be used to eliminate the effect of quantitative confounding factors. Quantitative confounding factors are physical activity and baseline values of the biochemical markers. Chi-square test will be used to compare the qualitative variables between the two groups and regression analysis is used to eliminate the effect of qualitative confounding.

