### Objectives and hypothesis

Primary aims of this clinical trial are the changes in anthropometric indices (including weight, BMI, hip circumference, waist-to-hip ratio, fat mass, muscle mass) and food addiction score. Secondary aims are changes in stress level, eating behavior, and serum levels of BDNF and LBP. A TRF is expected to improve these aforementioned indicators.

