### Inclusion and exclusion criteria

For the present study, 60 adult women with the following inclusion criteria will be included: aged 20–65 years; BMI: 26–39.9 kg/m^2^; willingness to participate in the study; confirmation of food addiction after obtaining the necessary score (at least 1 clinical score+ at least having 3 out of 7 criteria) from the YALE food addiction questionnaire; not having any diseases such as cancer, diabetes, newly hypothyroidism, renal or liver failure; non-pregnant or lactating; not perimenopause (women with irregular menstruation due to menopause or less than 2 years after amenorrhea); not participating in a weight loss diet during the last 2 months; and were not smokers.

Patients will be excluded if taking any antibiotics in the last 1 month or during the study; taking any medication affecting study outcomes regularly; using probiotic products (probiotic supplements, yogurt, cheese, cakes, biscuits, and probiotic pasta) continuously (more than once a week) in the last month or during the study; using weight-loss or appetite-suppressing medications; drinking alcohol at any levels before or during the study; and women with irregular menstruations. Also, we will exclude participants who refuse to continue the study, need antibiotics or have difficulties in fasting for 14 h a day in the intervention group.

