### Randomization, sequence generation, and concealment

Participants will be randomly allocated into two groups: the group receiving a low-calorie diet with the time-restricted feeding protocol or the control group receiving a low-calorie diet and will be followed up for 8 weeks. Stratified blocked randomization method is used to randomly assign people to two groups. The sequencing will be generated by one of the authors (AS) who is not going to assign participants into the study, so, allocation concealment will be ensured, as the author will not release the randomization code until the patient has been recruited into the trial by other authors (HI and [name]), which takes place after all baseline measurements have been completed. Participants are classified into overweight (26–29.9 kg/m^2^), grade 1 (30–34.9 kg/m^2^), and grade 2 obesity (35–39.9 kg/m^2^) based on BMI and randomly assigned to one of the control or TRF groups. Separate randomization is performed within each group for each BMI class. The size of the blocks is 4, two allocations are given to TRF group (A) and two allocations to Control Group (B). Six different permutations of AABB, ABAB, BBAA, BABA, ABBA, and BAAB will be created.

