### Intervention

In this study, patients receive the relevant diets for 8 weeks based on the group they are placed in. In both groups, after calculating the amount of calories required by each individual using the Mifflin formula [30] as much as 300–500 kcal will be deducted from the total energy required for each person (a 500 kcal reduction from calories is using for most of the cases, except for whom the calorie falls below 1200 kcal/d with 500 kcal reduction. In these cases, 300–400 kcal reduction will be used.) and accordingly, the low-calorie diet plan is given to each individual. The diet in each group will consist of 50–55% carbohydrates, 15–20% protein, and 30% fat. Patients in the TRF group will receive their meals from 10 h a day from 10 am to 8 pm [31] while the control group will have less than 12 h fasting.

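### For weight and food addiction score, the only test explicitly of change is within-arm, although the trial is sized on a between-arm difference in weight loss

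*Protocol article*

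**What the plan says.** All places are in the protocol article.

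- **Statistical analysis.** Within arms: "Paired *t* test will be used to compare the mean of quantitative variables with normal distribution in each group between the beginning and the end". Later in that sentence comes the between-arm test: "the *t* test will be used to compare their mean between the two groups at the beginning and end of the study". Wilcoxon and Mann-Whitney tests replace these for non-normal variables. Repeated-measures ANOVA is kept for variables measured three times. Covariance analysis follows, and its covariates are listed: "Quantitative confounding factors are physical activity and baseline values of the biochemical markers".
- **Study outcomes.** "Primary outcomes of this clinical trial are the changes in anthropometric indices", with food addiction score added to the list.
- **Sample size.** The calculation uses a 2.3 kg difference in weight loss between TRF and control.
- **Objectives and hypothesis.** The hypothesis names no comparator: "A TRF is expected to improve these aforementioned indicators".
- **Randomization and Intervention.** The arms are "the group receiving a low-calorie diet with the time-restricted feeding protocol or the control group receiving a low-calorie diet". For both, "as much as 300–500 kcal will be deducted from the total energy required for each person".
- **Inclusion and exclusion criteria.** Entry, judged by questionnaire score, requires "confirmation of food addiction after obtaining the necessary score (at least 1 clinical score+ at least having 3 out of 7 criteria").

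**The concern.** The trial asks whether restricting the eating window adds anything to a low-calorie diet. Only a comparison of the two arms can answer that. A before-after change inside the TRF arm mixes any window effect with the shared diet and the shared twice-weekly calls. For the food addiction score it may also include regression to the mean, because women enter by scoring above a threshold.

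The plan lists within-arm and between-arm tests side by side and does not say which one carries the conclusion. The between-arm test it describes is on raw values, not on change. The hypothesis is worded as improvement under TRF. A significant paired test in the TRF arm could therefore be read as meeting the hypothesis while the randomised comparison shows nothing. Significance in one arm and not in the other could likewise be taken for a difference between arms.

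**Working it through.** **1. The plan's own figure.** The 26 per group cannot be reproduced, because no SD is given. Solving for the SD, with two-sided alpha 0.05 and 80% power:

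SD = 2.3 / [(1.960 + 0.842) × √(2/26)] = 2.3 / 0.777 = 2.96 kg (2.90 kg with the t distribution).

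This is an implied value, so a range of 2.5 to 4.0 kg is used below.

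**2. Which test addresses the primary change?**

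| Planned method | Applies to weight and food addiction score? | Tests change? | Compares arms? |
|---|---|---|---|
| Paired t / Wilcoxon | yes | yes | no |
| t test / Mann-Whitney at beginning and end | yes | no, raw values | yes |
| Repeated-measures ANOVA | not shown: the only week-4 assessment described is dietary intake | – | – |
| Covariance analysis | their own baselines are not among the named covariates | not as described | yes |

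The quantity behind the sample size, the between-arm difference in weight loss, is not explicitly tested.

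**3. Paired test on weight with no window effect.** Noncentrality = (loss / SD) × √26; critical t (25 df) = 2.060. For a 2 kg loss and SD 2.96: 0.676 × 5.099 = 3.45, which gives 0.91. The diet-driven loss is an assumption. Probability that the TRF arm shows a significant loss:

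| SD of change | 1 kg | 1.5 kg | 2 kg | 3 kg |
|---|---|---|---|---|
| 2.5 | 0.50 | 0.84 | 0.98 | >0.99 |
| 2.96 | 0.38 | 0.70 | 0.91 | 0.999 |
| 4.0 | 0.23 | 0.45 | 0.69 | 0.96 |

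**4. TRF significant, control not.** With equal true loss in both arms the chance is p(1 − p). It peaks at 0.50 × 0.50 = 0.25 (1 kg, SD 2.5). At 2 kg and SD 2.96 it is 0.08.

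**5. Food addiction score with no effect of diet or window.** This step assumes that the eligibility score is also the baseline, that scores are normal, and that test-retest reliability is r. Write q for the share above the cut-off, c for the cut-off and m = φ(c)/q. The expected fall is (1 − r)m, in SD units. With q = 0.262 (the Background's prevalence in Iranian women with obesity), c = 0.637 and m = 1.243.

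The variance of baseline scores after selection is v = 1 + cm − m² = 0.247, and the SD of change is √[(1 − r)²v + 1 − r²].

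For r = 0.8: fall 0.2 × 1.243 = 0.25; SD of change 0.608; noncentrality (0.249 / 0.608) × 5.099 = 2.09; probability 0.52.

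| r (assumed) | Fall (SD) | Paired test significant |
|---|---|---|
| 0.9 | 0.12 | 0.28 |
| 0.8 | 0.25 | 0.52 |
| 0.7 | 0.37 | 0.71 |
| 0.6 | 0.50 | 0.84 |

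Over the Background's prevalence range of 19 to 56.8% and the same reliabilities, the probability runs from 0.12 to 0.93.

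**6. Between-arm tests.** In 20,000 simulated trials with no window effect, the between-arm t test rejected in about 5% of runs (0.048 to 0.053), on final weight or on change. Validity is intact; sensitivity is not. With a true difference of 2.3 kg, SD of change 2.96, an assumed baseline weight SD of 8 to 12 kg and change independent of baseline, power is about 10 to 15% on final weight and about 78% on change.

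**The case against.** The sentence that plans the paired test also plans a between-arm test, and covariance analysis follows. Order in a sentence sets no hierarchy. The Sample size section already names the right contrast. The shared diet is the feature that isolates the eating window: effects of the diet, the calls and regression to the mean fall on both arms and cancel in the randomised comparison. Nothing says that a within-arm result will support a TRF claim. This is a condensed article, and the choice of confirmatory test is often left to an analysis plan.

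Much of this stands. A reader might infer that no valid between-arm test is planned, that regression to the mean biases the trial, or that the paired tests are bound to show improvement. The documents support none of these. The planned between-arm test keeps its 5% error rate, and the probabilities above depend on a weight loss, an SD and a reliability that the article does not give. The regression-to-the-mean figures are rougher still. Entry is a composite rule, the trial also enrols overweight women and recruits through a clinic, and the article does not say that the eligibility score is the baseline.

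What the objection does not remove is a mismatch in the stated methods. Outcomes and sample size are framed as change, while the between-arm test is described on raw values and the named covariates omit baseline weight and baseline food addiction score. That is a method fixed badly, not a detail left out.

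**Conclusion.** The point holds as a mismatch between objectives, sample size and analysis. For weight and food addiction score, change is explicitly tested only within arms, where it cannot be credited to the eating window.

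Under the assumptions shown, a significant within-arm weight loss with no window effect has a probability of about 69 to 98% at a 2 kg diet-driven loss. At 1 kg this drops to 23 to 50%, so such a result is likely rather than certain. Regression to the mean adds to the within-arm fall in food addiction score only if the eligibility score serves as baseline. The randomised comparison stays unbiased by either mechanism, but as described, on raw end values, it would have little power for weight.

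**What to change.** - **Objectives and hypothesis:** state each objective as the TRF-minus-control difference in change from baseline to week 8.
- **Statistical analysis:** make that between-arm comparison the sole basis for conclusions about TRF, preferably by ANCOVA of the week-8 value on arm and the outcome's own baseline value. Baseline weight and baseline food addiction score then join the covariates for their own outcomes.
- **Within-arm results:** report mean changes descriptively, not as tests of TRF.

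A second baseline completion of the food addiction questionnaire is not needed. The randomised comparison is valid without it, and adding it during enrolment would leave two baseline definitions for a primary outcome.

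The cost is wording in two sections and a little analysis, with no new data. The Protocol amendments section requires a formal amendment for changes of objectives that may affect study conduct, so the rewording may need that route. The article reports the trial as still enrolling, so the change could be made before analysis.

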### Sample size

The number of participants was calculated based on the changes in body weight, as a primary outcome. The number of participants in this study was determined by the difference in weight loss between the TRF and control groups of 2.3 kg [28]. This difference has a probability of 95% (*α*=0.05) and a power of 80% (*β*=20%), which is statistically significant. Using this method, each group was estimated to have 26 participants, so that after taking into consideration 20% attrition, every group will be comprised of 30 participants. Collectively, 60 women with overweight or obesity and food addiction will be enrolled.

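### The trial is sized and defined on change in weight, but the stated between-group test compares raw means and the named covariates omit the baseline value of the primary outcomes, leaving power far below 80%

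*Protocol article*

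**What the plan says.** **Outcome and sizing.** The Sample size section states: "The number of participants was calculated based on the changes in body weight, as a primary outcome". The effect is a "difference in weight loss between the TRF and control groups of 2.3 kg", with α = 0.05, 80% power, 26 per arm, and 30 per arm after an allowance for 20% attrition. No SD is given. The Study outcomes section agrees: "Primary outcomes of this clinical trial are the changes in anthropometric indices". Food addiction score is also primary. The objectives section words these outcomes as changes too.

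**Analysis.** The Statistical analysis section plans:
- a paired t test of start against end within each arm;
- a t test that "will be used to compare their mean between the two groups at the beginning and end of the study", with Wilcoxon and Mann-Whitney tests as the non-normal counterparts;
- repeated-measures ANOVA for variables measured at the start, week 4 and week 8;
- ANCOVA for quantitative confounders, which it lists: "Quantitative confounding factors are physical activity and baseline values of the biochemical markers";
- regression for qualitative confounders, which it does not list.

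**Allocation.** Randomization is in blocks of 4 within three BMI classes: "Separate randomization is performed within each group for each BMI class". No model names BMI class.

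**The concern.** The only analysis stated to use each woman's own change is the paired test, and it does not compare the arms. The stated comparison of arms uses the variable's level at each time point. In a population with BMI 26–39.9, week-8 weight mostly reflects how heavy a woman was at entry, and that variation buries a 2.3 kg effect.

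ANCOVA would remove the problem if it included baseline weight. The covariate list instead names baseline values only for the biochemical markers, BDNF and LBP, which are secondary outcomes. Baseline adjustment is thus provided for some secondary outcomes and not for the primary ones.

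At stake is a trial that would probably miss the effect it was built to detect. The comparison of end means is not biased, since allocation is random. The loss is one of precision.

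**Working it through.** **Inputs from the protocol.** Difference 2.3 kg; α = 0.05 (taken as two-sided, since sidedness is not stated); power 80%; 26 per arm before attrition; 30 enrolled per arm, so 30 × 0.8 = 24 after 20% loss.

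**Assumptions.** SD of week-8 weight 8–15 kg, and mean height 1.60 m in the simulations. The documents give neither.

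**1. The plan's own figure.** The 26 cannot be reproduced without an SD, so solve for the SD it implies:

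SD of change = 2.3 × √(26/2) / (1.960 + 0.842) = 2.3 × 3.606 / 2.802 = 2.96 kg.

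With the noncentral t, the standardized difference at 80% power is 0.792, so SD = 2.3 / 0.792 = 2.90 kg. The trial's 80% therefore belongs to an outcome with an SD of about 2.9 kg.

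**2. The t test as stated, on week-8 means.** Standard error = SD × √(2/n). For SD 10 kg and n = 26 this is 10 × 0.2774 = 2.77 kg. The ratio is 2.3 / 2.77 = 0.83 and power ≈ Φ(0.83 − 1.96) = 13%. Noncentral t results, ignoring stratification:

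| n per arm | SD 8 kg | SD 10 kg | SD 12 kg | SD 15 kg |
|---|---|---|---|---|
| 24 | 16.4% | 12.2% | 10.0% | 8.2% |
| 26 | 17.4% | 12.9% | 10.4% | 8.4% |
| 30 | 19.5% | 14.1% | 11.3% | 9.0% |

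The difference detectable with 80% power at n = 26 is 0.792 × SD: 6.3 kg at SD 8 kg and 9.5 kg at SD 12 kg. Even an implausibly small SD of 5 kg gives only 37% power at n = 26. Keeping 80% would need a week-8 weight SD near 2.9 kg, which the eligible BMI range rules out.

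**3. Effect of the stratified allocation.** Balancing BMI class between arms makes the true variability of the difference smaller, but an unadjusted t test still takes its standard error from the full spread of weight. The standard error is overstated and the test is conservative. Simulations used 26 per arm, blocks of 4 within the three classes and a change SD of 2.9 kg:
- BMI uniform on 26–39.9 and every height 1.60 m: about 12–13% power if allocation were unstratified, about 0.6% with stratification.
- The same with a height SD of 0.05–0.07 m: about 2–3%.
- A BMI distribution narrower than uniform but still spanning the three classes: up to about 5%.
- I also tried BMI uniform on only 26–35 or 28–36, with height fixed or with SD 0.06 m. Power was about 8–14%, because class then explains less of the spread. This is still below the unstratified value in each case.

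**4. Adding BMI class alone.** With BMI uniform on 26–39.9 and a height SD of 0.06 m, the SD of weight within class is about 7.2 kg. Power is then 20% at n = 26 and 23% at n = 30.

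**5. Adding the baseline value.** With equal variance at both times, correlation ρ = 1 − 2.96² / (2 × SD²). At SD 10 kg, ρ = 1 − 8.76/200 = 0.956 and the residual SD is 10 × √(1 − 0.956²) = 2.93 kg. Power is 79% at n = 26 and 85% at n = 30, and is nearly the same for SD 8 or 12 kg. With BMI class also in the model, simulation gives about 78–79% at n = 26.

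**The case against.** **The wording might mean change.** An author could have intended a comparison of mean changes. The text does not allow it: the comparison is also made at the beginning, when no change exists.

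**Other clauses might cover it.** Repeated-measures ANOVA would use the baseline value if weight were measured three times. The text describes a week-4 assessment only for dietary recall. The timeline figure is not shown, so a week-4 weight cannot be wholly excluded, but nothing in the text supports one. The regression for qualitative confounding could include BMI class. It names no factor, and step 4 of the working shows that class alone would not restore power.

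**An article condenses the plan.** This stands in part. Silence about BMI class in the model could be left to a fuller document. The t test on means and the closed list of quantitative covariates are positive statements, and the point rests on those.

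**Stronger readings to avoid.**
- A reader might fix power at 12%. That figure needs an SD of about 10–11 kg, which the documents do not give, and it ignores the stratification.
- A reader might infer that week-8 physical activity will be a covariate, since "Physical activity questionnaire will be completed for them at baseline and week 8". The analysis section does not say which value is used, and nothing shows that the intervention alters activity.
- A reader might infer that efficacy will be claimed from the paired tests. The article also plans between-group tests and does not say this.

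**Conclusion.** The concern holds. The stated between-group test does not match the outcome on which the trial was defined and sized, and the named covariates do not repair it for the primary outcomes. For weight, power for 2.3 kg is about 8–20% if the week-8 SD is 8–15 kg and stratification is ignored. With the actual stratified allocation and an unadjusted test it is lower still: about 1–5% where BMI spreads widely over the eligible range, and somewhat higher where it does not.

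The exact figure depends on assumed weight, height and BMI distributions. The conclusion does not, because no plausible weight SD comes near the 2.9 kg required. The 80% comparator is itself inferred, since the protocol states no SD of change. The mismatch applies equally to the other primary outcomes, but the documents give no figures from which to size it there.

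**What to change.** In the Statistical analysis section, state the primary between-group analysis as ANCOVA of the week-8 value on arm, the baseline value of the same outcome, and BMI class (26–29.9, 30–34.9, 35–39.9). Report the adjusted difference with its 95% CI. Use the same model for the other continuous outcomes. If physical activity stays as a covariate, specify its baseline value. Present within-arm changes descriptively only. State the SD of change used in the Sample size section.

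The cost is wording. Weight and BMI class are already recorded at baseline, and no visit or participant is added. The model spends three degrees of freedom beyond arm (one for the baseline value, two for BMI class), or four with physical activity. The article reports the trial as still enrolling, so the change should be documented before any outcome data are compared by arm.
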